### 2.7. Patient Selection

Eligible patients will be screened by the treating medical oncologist. Prior to initiation of lenvatinib treatment, physical exam and blood sampling will be performed and vital signs, weight and performance status will be assessed to evaluate whether patients are eligible for the treatment and study. The first 12 patients conforming to inclusion and exclusion criteria (Table 2) agreeing to participate will be enrolled in the study.

### 2.8. Study Procedures

#### 2.8.1. Lenvatinib Treatment

Standard-of-care lenvatinib treatment will be provided to all patients included in this study for a duration of 6 or 12 weeks. A starting dose of 20 or 24 mg daily will be given in oral capsules. Dose reductions or interruptions will be induced at the treating physicians’ discretion in case of intolerable adverse events despite optimal management. In case of missed or interrupted administrations of lenvatinib, rescheduling of study procedures will be considered.

#### 2.8.2. Biopsy

A biopsy will be performed at baseline and an additional biopsy will be performed in the same lesion after 6 weeks of lenvatinib treatment. Lesions should be accessible for biopsy with low risk of severe side effects to the patients. Identification of the target lesions depends on the discretion of the treating physician. Biopsied tissue specimens will be evaluated with genomic, transcriptomic and protein-based research techniques to analyze whether alterations in molecular expression occur post-lenvatinib treatment and if treatment response is related to genetical profiles.

#### 2.8.3. I-124 Dosimetry Procedures

For cohort 1, rhTSH-stimulated I-124 dosimetry will be performed at baseline and after 6- and 12-week lenvatinib treatment. For cohort 2, rhTSH-stimulated I-124 dosimetry will be performed at baseline and at the most optimal interval observed in cohort 1 (either after 6- or 12-weeks lenvatinib treatment). Patients continue lenvatinib treatment during the procedures. Patients adhere to a low iodine diet 7 days prior to I-124 administration until 24 h post-administration. rhTSH injections will be given to the patient at home during 2 consecutive days (0.9 mg i.m.) prior to I-124 administration. Thyroid hormone (over)substitution may be continued. On the third day, but before administration of I-124, serum TSH and free thyroxine (fT4) will be measured as well as beta-human chorionic gonadotropin (HCG) in women of child-bearing potential. A total of 37 MBq (±10%) I-124 will be administered orally if TSH levels are >30 mU/L and beta-HCG is negative.

I-124 dosimetry procedures include:I-124 PET/CT
Pre-treatment dosimetry with PET/CT will be performed according to Jentzen et al. [26] This approach requires two PET/CT scans at 24 ± 6 and 96–120 h post-administration.
Activity in blood and the whole body
To assess toxicity of the bone marrow and lungs, the activity in blood samples and the whole body is determined according to Jentzen et al. [27] One heparinized blood sample of 2 mL is withdrawn from the patient and whole body counts measured at 2 ± 0.5, 24 ± 6 and 96–120 h post-administration. Whole body counting is performed using an uncollimated gamma camera detector.

Dosimetry procedures may be rescheduled up to 1 week when (1) patients fail to comply with the low iodine diet, (2) iodine is accidently administered or ingested (except for iodinated contrast), (3) delivery of I-124 is hampered or (4) PET/CT acquisition and assessment of blood counts and whole body retention is not possible due to failure or maintenance of the hardware and corresponding software. 

#### 2.8.4. I-131 Therapy

The redifferentiation effect will be evaluated by quantification of RAI uptake and assessment of corresponding expected dose to lesion and organs at risk per administered GBq I-131 [Gy/GBq]. Patients are eligible for I-131 therapy with MTA (maximized at 7.4 GBq) if:A clinically meaningful lesion dose is expected: ≥20 Gy in at least one lesion;Acceptable toxicity is expected: blood dose ≤2 Gy and 48 h post-administration body retention ≤3.0 GBq–4.4 GBq (with and without lung metastases).

If considered effective and safe, lenvatinib will be discontinued and standard-of-care I-131 therapy will be given after rhTSH stimulation. Patient preparations are identical to the preparations performed prior to the I-124 dosimetry procedures, including rhTSH administration and dietary restrictions. After ingestion of I-131, patients stay within the hospital considering radiation protection measures and are monitored during their stay until dose-rates are below the local limit for discharge. 

#### 2.8.5. Post-Therapeutic Dosimetry

Post-therapeutic dosimetry is performed for dose verification. Serial SPECT/CT scanning is performed according to Wadsley et al. [28] to determine actual absorbed lesion doses after I-131 therapy. The approach defined by the European Association of Nuclear Medicine (EANM) is used to verify absorbed doses to the blood and whole body retention. [29] Patients undergo SPECT/CT at 24 ± 6, 48 ± 6, 72 ± 6 and 144 ± 24 h post-administration. One heparinized blood sample of 2 mL is withdrawn from the patient and whole body counts are measured at 2–4, 6 ± 1, 24 ± 6, 96 ± 12 and 144 ± 24 h post-administration. 

Quantification of RAI uptake and assessment of corresponding expected absorbed lesion dose per administered GBq I-131 [Gy/GBq] will be determined by dedicated dosimetry software. The absorbed dose to the blood and whole body retention is determined using the approach defined by the EANM [29].

#### 2.8.6. Quality of Life Assessment

QoL is assessed according to 4 different questionnaires:THYCA-QoL: disease-specific health-related QoL questionnaire for thyroid cancer survivors [30];RAND-36 V2.0 (SF36-II): a validated translation in Dutch of the Short Form health survey (SF36-II) comprising 36 questions yielding a 9-scale profile of function health, wellbeing and psychometrically based physical and mental health [31];EQ-5D-5L: EuroQol 5-dimensional 5-level questionnaire: indexing health status including a single visual analogue scale (VAS) [32];DT&PL: an 11-point VAS including a 35-item problem list. We will only use the VAS, since the 35-item problem list mostly overlaps with the content of the other questionnaires [33].

Patients are asked to fill in the surveys at baseline and every time an F-18 FDG PET/CT is performed (at 6, 12, 24 and 36 weeks). In cohort 2B, QoL will also be assessed at 6 weeks. For all patients eligible for I-131 therapy, QoL will be assessed at the last SPECT/CT (Table 1).

#### 2.8.7. Follow-Up

Treatment response will be assessed using standard-of-care (unstimulated) F-18 FDG PET/CT and thyroglobulin levels at 12, 24, 36 and 48 weeks after initiation of lenvatinib treatment as part of the routine evaluation every 12 weeks. This PET/CT replaces the routinely performed contrast-enhanced whole-body CT scan as iodinated (intravenous) contrast media interfere with iodine (I-124, I-131) uptake in thyroid (cancer) tissues. Scans are performed according to EANM guidelines for tumour PET imaging 2.0 [34] and evaluated following PET Response Criteria in Solid Tumors (PERCIST 1.0) [35].

For this study, an additional F-18 FDG PET/CT will be performed at 6 weeks to evaluate the effect of lenvatinib treatment. In all patients treated with I-131, an evaluation will be performed 6 months after I-131 therapy. For cohort 1 this coincides with the standard-of-care follow-up 36 weeks after start of lenvatinib. In cohort 2 this could mean that if the evaluation of cohort 1 confirms that 6 weeks of lenvatinib treatment is the optimal duration, an additional F-18 FDG/PET will be performed at 30 weeks.

### 2.9. Data Analysis and Statistics

The variables obtained before lenvatinib treatment will be compared with those during or after treatment using paired non-parametric tests corresponding to the type of outcome measures. The fraction of patients eligible for I-131 therapy and numeric dosimetry results will be compared using McNemar’s test and the Wilcoxon-signed rank test, respectively. Multiple-comparison correction will be applied when necessary. We will use descriptive statistics to describe metabolic and biochemical treatment responses, incidence and severity of toxicities and quality of life.

An interim analysis is planned when all patients of cohort 1 have finalized their last I-124 PET/CT and a decision is made whether to pursue with I-131 therapy. The interim analysis will be conducted by an independent committee. Based on the primary endpoint of the study (the fraction of patients eligible for I-131 therapy) and I-124 dosimetry results pre- and post-lenvatinib treatment, the optimal treatment duration is determined (either 6 or 12 weeks). Furthermore, incidence and severity of toxicities are evaluated to assess cumulative toxicity of lenvatinib and subsequent I-131 therapy.

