The focus in this trial will be to evaluate the ability of lenvatinib to redifferentiating RAI-refractory DTC to an extent that functional RAI uptake is restored and I-131 therapy is justified. We will objectify this by quantitative molecular imaging and will predict efficacy and toxicity of radioiodine-131 based on dosimetry. We hypothesize that at least 40% of the patients will show sufficient redifferentiation for subsequent meaningful I-131 therapy. Since this would imply reduced lenvatinib treatment duration and since I-131 therapy is generally better tolerated by patients, this potentially leads to a new, less toxic treatment approach with higher quality-of-life.

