### 2.4. Sample Size Calculation

The study requires 12 patients of which 5 (42%) are expected to show meaningful renewed uptake of radioiodine to confirm that the real fraction is at least 15% (binomial distribution 95%-confidence interval: 15.2–72.3%).

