### 2.6. Study Endpoints

The primary endpoint of the study is the fraction of RAI-refractory thyroid cancer patients that is eligible for I-131 therapy after 6- or 12-week lenvatinib treatment to an extent that clinically meaningful tumor radiation doses can be safely delivered with acceptable I-131 doses as determined by I-124 dosimetry of both lesions and healthy organs at risk.

Secondary endpoints include:Extent of RAI uptake at baseline and after 6- or 12-week lenvatinib;Optimal duration of lenvatinib treatment (6 weeks or 12 weeks) for maximum redifferentiation;Agreement between expected absorbed dose per lesion predicted by I-124 PET/CT dosimetry and actual absorbed dose per lesion determined by intra-therapeutic I-131 single photon emission computed tomography (SPECT)/CT dosimetry in patients in which I-131 therapy is warranted;Metabolic and biochemical treatment response using F-18 FDG PET and unstimulated (thyroid-stimulating hormone (TSH)-suppressed) Tg levels, respectively;Progression free survival, best objective response and overall survival;Incidence and severity of toxicities according to the Common Terminology Criteria for Adverse Events (CTCAE) 5.0;Quality of life (QoL).

An explorative endpoint of this study is to evaluate alterations at the transcriptional and translational level in biopsied tumor lesions before and after 6-week lenvatinib treatment and to determine whether treatment response is related to genetical profiles.

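### Section 2.4 sizes the trial on a one-sample interval against 15%, but the only method section 2.9 names for the primary fraction is McNemar's test of change from baseline

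*Protocol article*

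**What the plan says.** Section 2.6 defines the primary endpoint as a single post-treatment fraction: "The primary endpoint of the study is the fraction of RAI-refractory thyroid cancer patients that is eligible for I-131 therapy after 6- or 12-week lenvatinib".

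Section 2.4 sizes the trial on that fraction alone: "The study requires 12 patients of which 5 (42%) are expected to show meaningful renewed uptake of radioiodine". The stated aim is "to confirm that the real fraction is at least 15" per cent, supported by a "binomial distribution 95%-confidence interval: 15.2–72.3" per cent. The Background gives the expected rate: "We hypothesize that at least 40% of the patients will show sufficient redifferentiation for subsequent meaningful I-131 therapy".

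Section 2.9 first sets out a before/after comparison: "The variables obtained before lenvatinib treatment will be compared with those during or after treatment using paired non-parametric tests". It then names the method for the fraction: "The fraction of patients eligible for I-131 therapy and numeric dosimetry results will be compared using McNemar’s test" (the Wilcoxon signed-rank test is for the numeric results). The same section calls the eligible fraction the primary endpoint. It names no other method for it and mentions neither the 15% reference nor the binomial interval. It gives no McNemar version, significance level or sidedness.

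**The concern.** The question that justified 12 patients is whether the post-treatment fraction exceeds 15%. McNemar's test addresses whether as many patients gain eligibility as lose it. If almost nobody is eligible at baseline, rejecting that null shows that the fraction rose above roughly zero. It does not show that the fraction exceeds 15%.

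The two methods can also point in different directions at the very result the trial was sized for. A report could then cite either the interval or the test after the data are known. An analysis plan that followed section 2.9 literally would carry the mismatch forward.

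**Working it through.** **Inputs.** From section 2.4: n = 12, planned result 5, reference fraction 15%, 95% interval. From the Background: hypothesised rate 40%. Assumptions, because the article does not state them: two-sided 0.05 for McNemar's test, and 0 of 12 eligible at baseline, which is the most favourable case for that test.

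**1. Reproduce the plan's figure.** The Clopper-Pearson lower limit L for 5 of 12 solves P(X ≥ 5 | 12, L) = 0.025, and the upper limit is found in the same way from the other tail. The result is 15.17% to 72.33%, which matches the stated 15.2–72.3%. For 4 of 12 the lower limit is 9.9%, so 5 is the smallest count that clears 15%. As a check, P(X ≥ 5 | 12, 0.15) = 0.0239, below 0.025.

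**2. McNemar's test at the planned result.** Let b be the number who gain eligibility and c the number who lose it. With none eligible at baseline and 5 afterwards, b = 5 and c = 0.

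- Exact two-sided: 2 × 0.5^5 = 0.0625.
- Continuity-corrected: (|5 − 0| − 1)²/5 = 16/5 = 3.20, p = 0.074.
- Uncorrected: (5 − 0)²/5 = 5.00, p = 0.025.
- Mid-p: 0.0625 − 0.5^5 = 0.031.
- Exact one-sided: 0.5^5 = 0.031.

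The first two are above 0.05 and the other three below it.

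**3. Where each version first passes 0.05, with c = 0.**

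| Gains b | Exact two-sided | Continuity-corrected | Uncorrected | Mid-p | Exact interval clears 15%? |
|---|---|---|---|---|---|
| 4 | 0.125 | 0.134 | 0.046 | 0.063 | No (9.9%) |
| 5 | 0.0625 | 0.074 | 0.025 | 0.031 | Yes (15.2%) |
| 6 | 0.031 | 0.041 | 0.014 | 0.016 | Yes (21.1%) |

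The exact and corrected versions need one more patient than section 2.4 does. The uncorrected version needs one fewer. Of these four, only mid-p has the same threshold.

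**4. Patients eligible at baseline.** Table 2 admits patients whose metastatic lesions are RAI-avid. Section 2.8.4 asks for the lesion-dose threshold in only one lesion, together with the toxicity limits. A baseline count above zero is therefore possible. If one of the five was already eligible, b = 4 and c = 0, and the first row of p-values applies: exact 0.125 and mid-p 0.063. The interval criterion is unaffected, because 5 of 12 are still eligible after treatment. If instead a sixth patient was eligible at baseline and lost eligibility (b = 5, c = 1), exact p is 0.219 and uncorrected p is 0.103.

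**5. Probability of disagreement under the stated assumptions.** With X ~ Bin(12, 0.40), P(X ≥ 5) = 0.5618 and P(X ≥ 6) = 0.3348. The difference is P(X = 5) = 0.5618 − 0.3348 = 0.2270, or 23%. This is the chance that the interval criterion is met while exact two-sided McNemar at 0.05 is not, with none eligible at baseline.

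**The case against.** The strongest reply is that the two methods answer different questions and may differ without contradiction. Section 2.4 holds the only success-type statement for the primary fraction. Section 2.9 describes change from baseline, for which McNemar's test is a natural choice with binary data. The version, level and sidedness are details that an article commonly leaves to the full protocol or analysis plan.

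Much of this stands, and it rules out several stronger readings.

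- A reader might infer that the trial could fail its own test. The article never makes a significant McNemar result the condition for success.
- A reader might infer that McNemar's test is not significant at 5 of 12. That is true for the exact two-sided and continuity-corrected versions only; the uncorrected, mid-p and one-sided exact versions fall below 0.05.
- A reader might infer that the choice between 6 and 12 weeks in cohort 1 needs significance in six patients. Section 2.6 lists "Optimal duration of lenvatinib treatment (6 weeks or 12 weeks) for maximum redifferentiation" as a secondary endpoint. Sections 2.5 and 2.9 have the duration selected from the eligible fraction and the dosimetry, with no significance requirement.
- A reader might infer that a multiplicity correction will tighten the threshold. A Bonferroni level of 0.025 for two comparisons would leave all the two-sided versions non-significant at 5 versus 0 (uncorrected p = 0.0253). But section 2.9 corrects only where needed and does not say that this applies to the primary fraction.

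The reply does not remove the mismatch itself. Section 2.9 is the analysis section, it identifies this fraction as the primary endpoint, and the one method it attaches to it does not test the 15% criterion. That is a named method that does not fit, rather than an omitted detail.

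**Conclusion.** The point holds in a limited form. The sizing criterion and the named analysis of the primary fraction test different hypotheses, and section 2.9 does not say which one governs the conclusion. At the planned 5 of 12, with none eligible at baseline, McNemar's two-sided p runs from 0.025 to 0.074 according to the version, so agreement with section 2.4 is left to an unstated choice. Any patient eligible at baseline makes it less likely.

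The 23% chance of disagreement is conditional on the exact two-sided version at 0.05, no patient eligible at baseline, and a true rate of 40%. Under mid-p or the uncorrected version, with none eligible at baseline, there is no disagreement at 5 of 12. The mismatch of hypotheses does not depend on any of these assumptions.

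**What to change.** In section 2.9, state that the primary analysis is the exact (Clopper-Pearson) 95% interval for the fraction of patients eligible for I-131 therapy after lenvatinib, judged against 15%, and that the criterion is met at 5 or more of 12. Label McNemar's before/after comparison as supportive, and fix its version, level and sidedness before the data are seen.

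The cost is a few sentences of wording. The sample size, study procedures and patient burden do not change.

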## 3. Discussions

In this trial, we evaluate the redifferentiation ability of lenvatinib in RAI-refractory DTC to restore impaired iodine uptake and retention by assessing functional RAI uptake pre- and post-lenvatinib treatment. Following I-124 dosimetry procedures, absorbed doses to lesions and organs at risk will be calculated to determine whether I-131 is deemed effective and safe. This proof-of-concept study poses a potential new treatment approach for RAI-refractory DTC patients by shortening the duration of lenvatinib treatment in combination with subsequent I-131 therapy, thereby potentially reducing severe toxicity and improving quality of life. 

Developments in the identification of RAI-refractory DTC by means of evolving molecular imaging and pathology is pivotal for optimizing current patient management. Assessment of the molecular landscape and altered signaling pathways can help in selecting treatment targets and may lead to a better selection of patients in which a redifferentiation effect is likely to be seen [9,36,37].

Quantification of RAI uptake by means of dosimetry poses the possibility to identify patients who redifferentiate after TKI treatment. Moreover, I-131 therapy can be initiated following a theranostic concept, thereby taking into account the RAI retention of lesions and organs at risk in time [38]. Leading guidelines state that treatments involving ionizing radiation should be individually planned and their delivery verified [39]. While it is standard-of-care in radiotherapy, personalized dosimetry has not yet been widely implemented in nuclear medicine. Estimating absorbed doses to lesions and organs at risk is a time- and resource-consuming process that is prone to errors. As it comprises multiple PET/CT or SPECT/CT measurements, it poses logistical challenges in clinical practice and increases patient and radiation burden. Besides that, there is currently no thorough evidence that dosimetry-based I-131 therapy is more effective than the standard practice approach in which empirical I-131 activities are given to the patient [40]. However, dosimetry is thought to be helpful in the management of more complex patients having a young age, advanced disease, extensive pulmonary metastases, renal insufficiency or failure, suspected recurrence, potential metastatic disease or a combination of these factors [41,42,43]. 

Rigorous and reproducible dosimetry methodologies are needed to facilitate comparison of dosimetry results among studies. To meet this need, we will adhere to the simplified protocols developed by Jentzen et al. for I-124 dosimetry [26,27], guidelines provided by the EANM for intra-therapeutic toxicity assessment [29], and follow initiatives of standardizing quantitative SPECT for dosimetry studies of I-131 treatment [44,45]. 

In the follow-up, we choose to replace the routine 12-weekly evaluation of lenvatinib treatment with contrast-enhanced CT by F-18 FDG-PET/CT. The use of contrast-enhanced CT would preclude diagnostic iodine-scintigraphy (including I-124 PET) and I-131 therapy as iodinated contrast interferes with RAI uptake. This would result in diminished RAI uptake measurements that is undesirable in this trial. Valerio et al. showed that F-18 FDG PET/CT correlates with the response of RAI-refractory DTC to lenvatinib and patient survival [46]. Objective responses are thereby comparable between the two modalities in the long-term and F-18 FDG PET/CT seems even able to predict the long-term response early [46]. Therefore, we see F-18 FDG PET/CT as at least an equivalent alternative to contrast-enhanced CT. 

This trial is aiming at treating patients with short-term lenvatinib treatment with potential subsequent I-131 therapy after identification of a redifferentiation effect. Toxicities of this treatment combination of therapy are not thoroughly investigated, although no cumulative toxicity has been described in comparable trials sequentially combining both selective and multitarget TKIs and I-131 therapy [16,17,18,19,20,21,22,23]. We expect that this treatment combination potentially will avoid severe toxicities that are observed in long-term lenvatinib treatment. The effectiveness of short-term lenvatinib treatment with subsequent I-131 therapy in comparison with long-term lenvatinib treatment is, however, yet to be determined. If our hypothesis that lenvatinib is able to redifferentiate RAI-refractory DTC to renew or increase RAI uptake can be confirmed, the currently established management of RAI-refractory DTC needs to be reconsidered. A combination of short-term lenvatinib treatment with subsequent I-131 therapy may then be preferred as this approach has great potential to reduce toxicity and increase quality of life in comparison to standard-of-care long-term lenvatinib treatment.

